### Intervention Group

The IG will receive telerehabilitation via videoconferencing (Zoom Video Communications Inc., San Jose, CA, USA) twice per week for 4 weeks, supervised by a physical therapist experienced in remote exercise rehabilitation and symptom monitoring. The program will consist of aerobic exercise (including marching on the spot and multi-directional stepping exercises with or without added arm movements, similar to a gym-based aerobics class) with intensity based on the participant’s level of breathlessness or fatigue, whichever is highest, aiming for 2 to 4 (“slight” to “somewhat severe”) on the 0 to 10 category ratio scale.^20^ A modified category-ratio scale will be used for assessing fatigue (Suppl. Material 1). Additionally, we will ask participants to rate their worst fatigue in the period 12 to 24 hours post-exercise using this scale. In situations where fatigue increases by >2 points from a participant's pre-exercise fatigue rating, intensity prescribed during the following session will be reduced to avoid future post-exertional malaise. Strength training will consist of exercises using body weight (eg, squats, sit-to-stand), hand weights using cans of food, bags of rice, etc. (eg, biceps curls, shoulder flexion/abduction, upright row), or resistance bands. Strength exercises will be performed in 1-minute intervals and will be based on the individual’s fatigue and dyspnoea. The exercise program will last for 40 minutes, approximately 25 minutes for aerobic training and 15 minutes for strength training and will be in groups no greater than 5 participants, who will always be visible on the computer screen. Participants will be able to see and converse with the physical therapist and other participants during the sessions in real-time through the videoconferencing technology. The specific resistance and aerobic exercises to be prescribed with possible progressions and regressions for each are presented in Supplemental Material 2.

#### Fidelity

To ensure that the intervention is delivered consistent with the protocol in this multi-site (4 sites) study, the chief investigator will regularly log into a telerehabilitation session at each site. Any deviations from the study protocol will be discussed immediately after the session so that the intervention is delivered uniformly at all sites.

#### Safety Considerations

At the initial assessment prior to the first exercise session, the physical therapist will do a safety check by visually scanning the participant’s environment. At the commencement of an exercise session, if concerning symptoms are evident, the participant will not undertake the session and will be asked to present to their general practitioner or the emergency department, depending on the severity of symptoms. During a session, if the participant experiences a change in symptoms or has severe breathlessness or fatigue, they will be advised to stop exercising. All participants will be asked to report any new symptoms or change in symptoms before they start an exercise session. If fatigue was worse after the previous session, the exercise intensity will be reduced by using more rests, lighter weights, slower pace, and/or modified exercises. Participants will be asked to have a working phone nearby and the physical therapist will have the participant’s phone number available in case the internet drops out. In the case of a serious adverse event the physical therapist will call emergency services immediately.

Education will be provided by the physical therapist at rehabilitation sessions. Topics will include strategies to manage fatigue; pacing with daily activities; staying physically active; managing anxiety and depression; and returning to work. The education will be based on the WHO Pamphlet *Support for Rehabilitation: Self-Management after COVID-19-Related Illness*^21^ (Suppl. Material 3) and participants will be referred to the Lung Foundation Australia (LFA) *Understanding Long COVID* booklet^22^ (Suppl. Material 4). At the end of the 4-weeks, participants in the IG will receive advice on continuing with physical activity. All participants will be invited to complete a survey to help the investigators gain insight into the participants’ experiences with telerehabilitation.

#### Participant Interviews

At the end of the intervention period, between 15 and 20 participants in the IG will be invited to take part in a semi-structured, 30-minute interview via videoconferencing technology to gain a deeper understanding of their experiences and opinions about telerehabilitation. Participants will be invited to undertake an interview irrespective of whether they completed 8 sessions of the intervention. The interviewer will be a clinician independent of the treating and research team and will ask questions about barriers and enablers to participation in telerehabilitation for people with PCS.

### Control Group

The control group will receive usual medical care as well as a copy of the WHO Pamphlet.^21^ At the end of the 4-week control period, participants in the control group will be invited to cross-over into the IG. The cross-over is to encourage recruitment since the advice from those with lived experience of PCS was that participants needed the option to receive telerehabilitation after the control period. Additionally, as research in telerehabilitation for PCS is currently very limited, the crossover will provide increased data on rehabilitation outcomes.

### Outcome Measures

Following recruitment, baseline outcomes will be collected at an initial videoconference assessment. At all follow-up assessment times (Figs. 1 and 2), the physical outcomes will be collected by a physical therapist who is blind to group allocation. Participants will be asked not to divulge their group allocation. Outcome measures are outlined below.

**Figure 1 f1:**
[figure not shown]
Study flow chart.

**Figure 2 f2:**
[figure not shown]
Study visits timeline.

#### Physical Outcomes

Exercise capacity will be measured using the 1-minute sit-to-stand test (1-minSTST)^23^ (primary outcome measure). The 1-minSTST is considered a measure of aerobic capacity and has a moderate correlation with 6-minute walk test distance.^24^ The 1-minSTST has been validated and is widely used across the age-span.^25^ Functional lower limb strength will be measured by the 5 repetition sit-to-stand test. Recent evidence demonstrates that the use of sit-to-stand tests using telehealth technology is safe, reliable, and valid.^26–29^

During screening, all participants will have previously completed a 1-minSTST with pulse oximetry monitoring, face-to-face under the supervision of a physical therapist in a post-COVID Respiratory Clinic to check for safety. During the study the sit-to-stand tests will be supervised via videoconferencing by an experienced physical therapist and will allow comparisons to be made under the same conditions at all assessment timepoints. While a 46 cm-height chair without arm rests is standard for these tests,^23^ a chair closest to this height (measured by the participant) will be used and the same chair will be used at each assessment.

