### Sample Size

A total of 42 participants will be required to have an 80% chance of detecting, as significant at the 5% level, a between-group difference of 3.5 repetitions in the 1-minSTST (primary outcome), which is the minimal clinically important difference, using a standard deviation of 4 repetitions.^23^ To account for a 15% dropout, 48 participants will be recruited.

The sample size for the semi-structured interviews will be approximately 15 to 20 participants. Interviews will continue until thematic saturation.

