### Statistical Analysis

Statistical analysis will be performed using IBM SPSS version 28 (IBM Corporation, Armonk, NY, USA). Intention-to-treat analysis of between-group changes at the end of the initial intervention/control period will use linear mixed effects model analysis of variance for the primary and secondary outcome measures, with adjustments for any statistically significant differences in baseline covariates between the groups. Maximum likelihood estimation through the linear mixed effects model analysis of variance will be used for missing data. Following an intention-to-treat analysis, a “per protocol” analysis will be undertaken using the same statistical methods. Post-hoc analyses will also be undertaken to establish characteristics of responders to the intervention. Analysis of the data from the cross-over group will use repeated measures analysis of variance to evaluate the within-group change due to the intervention. Data analysis at the 12-month follow-up will be exploratory. If adequate numbers in the control group do not cross-over to the intervention, a between-groups analysis will be undertaken. However, it is anticipated that the majority of participants in the control group will cross-over into the IG, in which case the analysis will evaluate the change from completion of the intervention to the 12-month timepoint. The level of significance for all outcomes will be set at an alpha of <0.05.

The semi-structured interviews will be transcribed and coded using NVivo 9 (QSR International, Melbourne, Vic., Australia). Thematic and descriptive qualitative analysis^40^ will be used to identify key themes regarding participant opinions, and perceived barriers and facilitators to participation in the telerehabilitation program. At least 3 investigators will review the coding to ensure it is insightful. Any discrepancies will be discussed by the research team and the coding revised accordingly.

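### The clinic screening 1-minSTST is a second pre-treatment measure of the primary outcome that the stated covariate rule would normally leave unused: a modest, avoidable loss of precision, not an error or a bias

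*Protocol article*

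**What the plan says.** Physical Outcomes in the protocol article states that at screening "all participants will have previously completed a 1-minSTST with pulse oximetry monitoring, face-to-face under the supervision of a physical therapist", and gives the place and purpose: "in a post-COVID Respiratory Clinic to check for safety". Outcome Measures places the trial baseline later and in another mode: "baseline outcomes will be collected at an initial videoconference assessment". The remote tests are kept alike on purpose. Video supervision "will allow comparisons to be made under the same conditions at all assessment timepoints", and for the seat, "a chair closest to this height (measured by the participant) will be used and the same chair will be used at each assessment".

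Statistical Analysis says that the intention-to-treat comparison at the end of the four-week period "will use linear mixed effects model analysis of variance for the primary and secondary outcome measures". It goes on to state how covariates are chosen: "with adjustments for any statistically significant differences in baseline covariates between the groups". The screening count is neither named nor excluded. Sample Size gives the evaluable number: "A total of 42 participants will be required to have an 80% chance of detecting" a difference of 3.5 repetitions with a standard deviation of 4, with 48 to be recruited.

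**The concern.** A pre-treatment value of the outcome is usually among its strongest predictors. One count from a one-minute test carries measurement error and day-to-day variation, and a second count taken before allocation can remove part of that from the residual variance. The clinic test precedes invitation and consent, so it cannot be affected by allocation and is a valid covariate even though it was done in a different setting.

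The stated rule works against this. It admits a covariate according to whether the arms happen to differ significantly, not according to whether it predicts the outcome. With random allocation that happens for a given covariate about one time in twenty. A predictor that the clinic visit already produces would therefore normally be set aside in a trial of 42 evaluable people. What is at stake is the width of the confidence interval for the primary result.

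**Working it through.** **1. The plan's own figure.** Inputs from Sample Size: difference 3.5, SD 4, 5% level (two-sided assumed), 80% power, 1:1 allocation. Per arm, n = 2 × (1.960 + 0.842)² × 4² / 3.5² = 20.5, so 21, or 42 in total. The stated number reproduces. Power at 21 per arm is 0.809 by the normal approximation and 0.790 by the noncentral t. This figure does not rely on the clinic count.

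**2. Model for the gain.** The documents give no correlations, so these are assumptions:
- R, reliability of a single test: 0.7 to 0.9.
- s, stability of true capacity between successive tests: 0.90 to 1.00.
- m, correlation between clinic and home-video performance beyond measurement error: 1.0 (no mode effect), 0.9 or 0.8.

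The correlations are then:
- video baseline with week 4: r_b = R·s
- clinic with video baseline: r_cb = R·s·m
- clinic with week 4: r_c = R·s²·m

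The share of week-4 variance explained by both counts is (r_b² + r_c² − 2·r_b·r_c·r_cb) / (1 − r_cb²). The residual-variance ratio, both counts against video baseline alone, is (1 − that share) / (1 − r_b²). Multiplying by 39/38 charges the lost degree of freedom. The equivalent sample size is 42 divided by the net ratio.

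**3. One cell in full** (R = 0.8, s = 0.95, m = 0.9). r_b = 0.76, r_cb = 0.684, r_c = 0.650. Share explained = (0.5776 + 0.4222 − 0.6756) / (1 − 0.4679) = 0.609. Ratio = 0.391 / 0.422 = 0.925; net 0.949. 42 / 0.949 = 44.2, a gain of about 2 participants.

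**4. The grid: net variance ratio (gain in participants).**

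| m | R | s = 1.00 | s = 0.95 | s = 0.90 |
|---|---|---|---|---|
| 1.0 | 0.7 | 0.85 (7.3) | 0.91 (4.3) | 0.94 (2.5) |
| 1.0 | 0.8 | 0.82 (9.0) | 0.91 (4.3) | 0.95 (2.1) |
| 1.0 | 0.9 | 0.80 (10.8) | 0.93 (3.0) | 0.98 (0.8) |
| 0.9 | 0.7 | 0.91 (4.3) | 0.94 (2.5) | 0.97 (1.4) |
| 0.9 | 0.8 | 0.90 (4.5) | 0.95 (2.2) | 0.98 (1.0) |
| 0.9 | 0.9 | 0.92 (3.5) | 0.98 (1.0) | 1.00 (0.0) |
| 0.8 | 0.7 | 0.94 (2.5) | 0.97 (1.4) | 0.98 (0.7) |
| 0.8 | 0.8 | 0.95 (2.3) | 0.97 (1.1) | 0.99 (0.3) |
| 0.8 | 0.9 | 0.97 (1.4) | 1.00 (0.2) | 1.01 (−0.4) |

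With no mode effect the gain is about 1 to 11 participants. With m at 0.8 to 0.9 it is about 0 to 4.5, with a negligible loss in the worst cell. Before the degree-of-freedom charge the gain is exactly zero when r_c = r_b × r_cb (for example 0.64 = 0.8 × 0.8).

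**5. What this means for power.** Sample Size does not say whether the SD of 4 is for raw scores, changes or residuals.
- If it is the residual SD after the video baseline, power goes from 0.79 to 0.81, 0.83 or 0.87 at variance ratios of 0.95, 0.90 or 0.80.
- If it is the raw-score SD, the video baseline alone already gives 0.89 (correlation 0.5) or 0.97 (correlation 0.7). A fully exchangeable clinic count raises these only to 0.92 and 0.99.

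**6. How the count must enter.** Suppose the model takes baseline and week 4 as responses, with group, time and their interaction. A main effect of the clinic count adds the same amount to a person's two values and cancels from the difference in change. A check on simulated data confirmed that the interaction estimate was identical and its standard error effectively unchanged. The gain appears only when week 4 is the outcome and both earlier counts are covariates.

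**The case against.** The strongest reply is that nothing here is wrong. Omitting an optional covariate creates no bias and no contradiction, and the 42 reproduces without it. That stands, and it limits the point to an efficiency suggestion.

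A second reply is that a condensed article leaves its covariate list to fuller documents. That stands for the list. It does not stand for the selection rule, which the article states and which a later plan would have to depart from in order to fix the clinic count as a covariate.

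A third is that the clinic test is a safety check, in another mode and with a chair that is not described, at an unstated interval before baseline and in patients who may be recovering naturally. This does not make the count invalid as a covariate, but it does lower its value, which is why the mode correlation is in the calculation. The stability floor of 0.90 is itself only an assumption, and a longer gap would bring the gain closer to zero.

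A reader might go further and infer that free precision is being discarded in a trial with no slack. The documents do not support that. They do not say that the repetition count is kept as trial data, or that study consent covers it. The gain may be nil, and whether power is tight depends on what the SD of 4 describes.

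**Conclusion.** The point holds as a modest, optional gain in precision. The stated rule would normally leave the clinic count out, and using it would most plausibly be worth about 0 to 4 of the 42 evaluable participants beyond the video baseline alone. The upper figure of about 11 needs reliability of 0.9, no change in true capacity between tests and no difference between clinic and video. At the other end the loss is under half a participant. All of this rests on assumed correlations, and the documents cannot narrow it. The priority is low. The firmer weakness is the significance-based rule itself, of which this is one concrete consequence.

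**What to change.** In Statistical Analysis, pre-specify before any unblinded look at the data that:
- the week-4 1-minSTST count is the outcome, and the video baseline count and, where recorded, the clinic screening count are fixed covariates regardless of their between-arm p-values;
- the clinic count is not added as a main effect to a baseline-and-week-4 group-by-time model, where it would change nothing;
- the video test remains the baseline from which change is described;
- a missing clinic count is replaced by the overall mean with a missing indicator, so that no one is dropped for lacking it.

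The cost is a sentence or two of text, one degree of freedom (a second if the missing indicator is needed), and recording the clinic count in the trial database under consent. If the clinic visit was long before baseline or the two modes agree poorly, the gain may be negligible.

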#### Cognitive Function

Cognitive function will be measured using the Montreal Cognitive Assessment suitable for remote assessment (MoCA-BLIND; MoCA Test Inc., Québec, Canada)^30^ and will be administered by a physical therapist. Three alternative MoCA-BLIND versions (Version 7.1, 8.2, and 8.3) will be used for repeat assessments to reduce a possible practice effect.

#### Patient Reported Outcomes

The following questionnaires will be emailed to the participant through REDCap and will be completed at each assessment timepoint (Fig. 2). Participants in both groups will be asked to complete a weekly symptom diary via REDCap.

HRQoL will be measured using the 36-Item Short-Form Health Survey (SF-36)^31^ which comprises 36 questions across 8 domains of health. Anxiety and depression will be measured using the Hospital Anxiety and Depression Scale^32^ and the Kessler Psychological Distress Scale (K6+).^33^ The Hospital Anxiety and Depression Scale is a 14-item validated questionnaire^34^ and the K6+ is a reliable and valid 6-item questionnaire.^35^ Fatigue will be measured using the 9-item Fatigue Severity Scale^36^ which measures both severity of an individual’s fatigue and the effect of fatigue on their activities of daily living. Respiratory symptoms will be measured using the Chronic Obstructive Pulmonary Disease Assessment Test.^37^ Although designed for people with chronic obstructive pulmonary disease, the Chronic Obstructive Pulmonary Disease Assessment Test is widely used for many respiratory conditions as a measure of the presence and severity of respiratory symptoms such as breathlessness, cough, chest tightness, and sputum production.

Composite outcomes will be measured using the COVID-19 Yorkshire Rehabilitation Scale (YRS-19)^38^ which is a comprehensive COVID-specific patient reported measure that provides a score for several outcomes related to the domains of “symptoms severity” and “functional disability”.

At the 12-month follow-up assessment, participants will be asked to complete all previous assessments as well as the return-to-work questions from the International Severe Acute Respiratory and emerging Infection Consortium (ISARIC) questionnaire.^39^ The 12-month follow-up is exploratory and will evaluate any ongoing effects of the intervention, as well as natural recovery in participants in the control group who did not cross-over.

### Sample Size

A total of 42 participants will be required to have an 80% chance of detecting, as significant at the 5% level, a between-group difference of 3.5 repetitions in the 1-minSTST (primary outcome), which is the minimal clinically important difference, using a standard deviation of 4 repetitions.^23^ To account for a 15% dropout, 48 participants will be recruited.

The sample size for the semi-structured interviews will be approximately 15 to 20 participants. Interviews will continue until thematic saturation.

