**Methods:**

The study will be a multi-site randomized controlled trial with assessor blinding. Participants with confirmed previous COVID-19 infection and persistent respiratory symptoms who attend a post-COVID respiratory clinic will be randomized 1:1 to either an intervention group of 4 weeks, twice-weekly pulmonary telerehabilitation or a control group of usual medical care. Participants in the control group will be invited to cross-over into the intervention group after the week 4 assessment. Primary outcome: exercise capacity measured by the 1-minute sit-to-stand test. Secondary outcomes: 5 repetition sit-to-stand test; Montreal Cognitive Assessment; COVID-19 Yorkshire Rehabilitation Scale; Chronic Obstructive Pulmonary Disease Assessment Test; 36-Item Short-Form Health Survey; Hospital Anxiety and Depression Scale; Fatigue Severity Scale; and the Kessler Psychological Distress Scale. Outcomes will be collected at baseline, after 4-weeks intervention or control period, after intervention in the cross-over group, and at 12-month follow-up.

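### Recruiting 48 does not cover a 15% dropout to 42: it leaves about 41 and covers at most 12.5%, a minor slip worth about one point of power

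*Protocol article*

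**What the plan says.** The Sample Size section of the protocol article gives the requirement first: "A total of 42 participants will be required to have an 80% chance of detecting", "as significant at the 5% level", a difference of 3.5 repetitions in the 1-minute sit-to-stand test, "using a standard deviation of 4 repetitions". It then adds the allowance for losses: "To account for a 15% dropout, 48 participants will be recruited". The abstract gives equal allocation ("will be randomized 1:1"), so 42 means 21 per arm.

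The section names no test or formula and does not say whether the 5% level is one-sided or two-sided. The Statistical Analysis section plans an intention-to-treat linear mixed effects model for the primary outcome, with maximum likelihood estimation for missing data.

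**The concern.** A dropout allowance is meant to leave the required number once the expected losses have occurred. Dropout is a fraction of those recruited, so the requirement has to be divided by one minus the dropout rate. The stated 48 looks instead like 42 increased by 15%, which takes the percentage of the smaller number and yields too few.

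This is the article's only numerical justification for the size of the randomised comparison, and a reader can check it in one line. If the target is too low, the trial would miss its own analysable number even when dropout runs exactly as planned. With about 21 per arm, one or two participants decide whether power is just above or just below 80%.

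**Working it through.** **Inputs.** From the Sample Size section: difference 3.5, SD 4 (standardised difference 3.5/4 = 0.875), level 5%, power 80%, required total 42, dropout 15%, target 48. From the abstract: 1:1 allocation. Assumption: a two-sided test, because the section does not say.

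**Step 1: reproduce 42.** The normal-approximation formula is n per arm = 2 × (z₀.₉₇₅ + z₀.₈₀)² × (SD/difference)².

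2 × (1.96 + 0.8416)² × (4/3.5)² = 20.50, rounded up to 21 per arm, 42 in total. This matches the plan exactly, and power at 21 per arm is 80.9%. A one-sided calculation gives 17 per arm (34 in total) and does not match, which supports the two-sided reading.

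**Step 2: check the dropout allowance.**

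- Remaining after 15% loss from 48: 48 × 0.85 = 40.8, against 42 required.
- Target that keeps 42: 42/(1 − 0.15) = 49.4, so 50. Check: 50 × 0.85 = 42.5.
- Apparent origin of 48: 42 × 1.15 = 48.3, rounded to 48.
- Largest dropout that 48 can absorb: (48 − 42)/48 = 6/48 = 12.5%.

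**Step 3: effect on power, same formula as Step 1.**

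| Analysable | Power, two-sided normal approximation |
|---|---|
| 21 + 21 (42) | 80.9% |
| 20 + 21 (41) | 79.97% |
| 20.4 per arm (40.8) | 79.8% |

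The loss is about one point. It is this small because rounding had already added a margin: the unrounded requirement is 2 × 20.50 = 41.0 in total, so 40.8 falls only about 0.2 of a participant below it.

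**Step 4: sensitivity only.** With a two-sample t-test (noncentral t distribution), power is 79.0% at 21 + 21, 78.0% at 20 + 21 and 80.9% at 22 + 22. The cost of the dropout slip is again about one point.

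**The case against.** The strongest reply is that nothing of substance changes. The 42 reproduces exactly, 48 is recognisably 42 plus 15%, and on the formula that yields 42 the power after planned dropout still rounds to 80%. The planned mixed model also uses the baseline measurement and all available observations, so a calculation on completers at follow-up is probably conservative.

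Most of this stands as an argument about size, but it does not make the sentence right: 48 less 15% is not 42, and nothing elsewhere in the article repairs it. The gain from the mixed model cannot be counted either. The sample size section takes no credit for it, and the article gives no correlation between baseline and follow-up from which to compute it.

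A reader might go further and infer that 42 is itself too small, because a t-test gives 79.0% at 42 and first exceeds 80% at 44. The document does not support calling that an error. The section names no test, 42 is the correct result of a standard formula, and the primary analysis is a mixed model. The t-test figures therefore cannot be presented as the power that the design delivers.

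Nor should the result be quoted as a loss of two to three points. That adds about one point from changing the formula to about one point from dropout. The lowest figure that might be cited, 76.9% on a t-test, needs only 40 analysable, and 40 of 48 is a loss of 8/48 = 16.7%, more than the stated 15%.

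**Conclusion.** The dropout sentence is wrong as written, and the consequence is minor. Recruiting 48 with 15% dropout leaves about 41, one short of the stated 42, and 48 covers at most 12.5%. On the plan's own formula, power falls from 80.9% to between 79.8% and 80.0%.

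The arithmetic on 48, 42 and 15% needs no assumption beyond dropout being a share of those recruited. The power figures assume a two-sided 5% test, equal arms, SD 4 and no gain from baseline adjustment.

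A reader might infer that the whole sample size justification fails or that the trial is materially underpowered. Neither follows: the 42 is sound, and only the step from 42 to 48 is at fault.

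**What to change.** Restate the sentence so that its figures agree. Any one of these would do:

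- 48 recruited allows for 12.5% dropout, leaving 42 analysable (80.9% power by the two-sided normal approximation).
- 48 recruited with 15% dropout leaves about 41 analysable, with power of about 80% on that formula.
- If both 42 analysable and 15% dropout are to be kept, the target is 50.

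It would help to name the formula and the two-sided level in the same sentence, so that 42 can be checked directly. The first two options cost one edited sentence and no participants. The third adds two recruits. None of them changes the design or the analysis.
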